### Power calculations

Power calculations were carried out using the simulation approach developed by Zhang *et al.*[49]. The assumptions for the power calculations were as follows: mean square error (MSE), baseline intercept, and trend equal to the observed pre-intervention values in each region; change in intercept = 0; alpha = 5%; 24 data points before and six after the intervention (N = 30 data points in total). Zhang and colleagues [49] recommend a plausible range of r = 0.1 to r = 0.5 for the autocorrelation parameter [AR(1)]. To assess sensitivity with respect to the strength of autocorrelation, we conducted the power calculations for r = 0.4 as well as very strong correlation of r = 0.8 (Table 3). A summary of the required effect sizes **Δ** (change in slope) to yield 80% power for the likelihood ratio test of the intercept and slope changes in each region are presented in Table 3 as both absolute and relative changes. With at least 30 time points and assuming moderate autocorrelation, we will have 80% power (α = 0.05) to detect annual% changes in total donations of 8.5% in the West, 5.6% in Quebec, 7.8% in Ontario, and 14.0% in the Atlantic Provinces.

**Table 3 T3:** **Power calculation**^
**1 **
^**for ITS study**

	**Δ**^ **3** ^**donation rate (per million population per six months)**		**Δ donation count (per year based on 2011 population size)**^ **3** ^		**%Δ donation count (per year relative to 2011)**^ **3** ^	
AR(1)^2^	r = 0.4	r = 0.8	r = 0.4	r = 0.8	r = 0.4	r = 0.8
West	0.47	0.70	10.0	14.9	8.5%	12.6%
Quebec	0.48	0.73	7.7	11.7	5.6%	8.5%
Ontario	0.64	0.95	17.1	25.4	7.8%	11.5%
Atlantic	1.25	1.87	5.9	8.8	14.0%	21.0%

^1^The assumptions for the power calculations were as follows: (a) mean square error (MSE), baseline intercept, and trend equal to the observed pre-intervention values in each region; (b) change in intercept = 0, (c) alpha = 5%; (d) 24 data points before and six after the intervention (N = 30 data points in total).

^2^AR(1) = autocorrelation parameter.

^3^Δ = required effect sizes (change in slope).

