### Outcome measures

The primary outcome measure for evaluation of the knowledge translation intervention will be total donation rate (defined as the total number of organ donors, NDD plus DCD combined) per million population (PMP) per six months. Although a change in the DCD rate might seem to be a more appropriate outcome measure, we chose the total donation rate for two reasons. First, there is a concern that increased use of DCD might lead to fewer NDD donors [42]. If our intervention was successful at increasing DCD donors but led to a reduction in NDD donors, this would not be considered a positive intervention that should be adopted. If this occurred, use of the DCD rate alone as the primary outcome could potentially mislead stakeholders that our intervention should be implemented. By using the total donation rate, we will judge our intervention to be successful only if total donors increase. We hypothesize that there will be an increase in the total donation rate that is driven by an increase in the DCD rate with a neutral or even positive effect on the NDD donor rate as has been recently seen in the province of Ontario [43]. Second, since routine use of DCD only resumed in 2006 in Canada, observed DCD counts were all zero until 2005 and too small thereafter (<5 per million) to allow stable analysis of six-month intervals as planned (only seven pre- and three post-intervention time points for analysis). In contrast, the number of time points available for NDD and total donations is at least 30 (24 pre-, six post-intervention). So from a statistical perspective as well, total donation rate is the preferred primary outcome. Secondary outcome measures will be DCD rate (PPM per year) and (NDD) rate (PPM per six months).

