### Analysis plan

The proposed method of analysis is a segmented linear regression autoregressive error model of the observed aggregate outcomes in each of four regions that comprise the 10 Canadian provinces: Atlantic Canada (New Brunswick, Nova Scotia, Prince Edward Island, and Newfoundland), Ontario, Quebec, and Western Canada (British Columbia, Alberta, Saskatchewan, and Manitoba). This approach is commonly used in health services research because it can tolerate fewer time points than autoregressive integrated moving average (ARIMA) models and is amenable to intuitive graphical presentation [41]. The first step of the analysis will be a graphical inspection of donation rates over time, at six-month intervals, in each of the study regions. The full model will be fitted by specifying a pre-intervention intercept and slope, and two parameters that represent the change in intercept and change in slope after introduction of the intervention. Maximum likelihood estimation will be used as it is considered one of the most appropriate methods of estimation for small samples with autocorrelated errors [44]. The analysis will adjust both parameter and variance estimates for autocorrelation. No adjustment for seasonal trends is anticipated.

The significance of the knowledge translation intervention will be evaluated using a likelihood ratio test of the change parameters. The null hypothesis is that both intercept and slope changes are zero; the alternative hypothesis is that at least one of intercept or slope change is non-zero. The immediate and gradual effect of the knowledge translation intervention will be estimated using confidence intervals for both absolute and relative change in the intercept and slope, using methods developed by Zhang *et al.*[45]. The overall effect, combining intercept and trend changes, will be estimated using the absolute and relative difference in the predicted post-intervention outcome versus the predicted outcome from the secular trend (counterfactual estimate) together with confidence intervals, using the methods developed by Zhang *et al.*[45]. As recommended, we will report 95% confidence intervals using the 99% critical value to account for the fact that time series with a small number of time points and large autocorrelation may produce artificially narrow confidence intervals.

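### The annual percentage changes in the power statement are changes per six-month step; on the plan's own time axis the detectable yearly changes are twice as large

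*Protocol article*

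**What the plan says.** All references are to the protocol article.

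- **Outcome measures:** the primary outcome is the total donation rate, "defined as the total number of organ donors, NDD plus DCD combined) per million population (PMP) per six months".
- **Analysis plan:** the first step is a "graphical inspection of donation rates over time, at six-month intervals, in each of the study regions". The segmented model adds "two parameters that represent the change in intercept and change in slope after introduction of the intervention" to the pre-intervention intercept and slope.
- **Power calculations:** the effect size is defined by the words "A summary of the required effect sizes Δ (change in slope) to yield 80% power for the likelihood ratio test", with no change in intercept, alpha 5%, and 24 + 6 = 30 data points. The text then claims 80% power under moderate autocorrelation "to detect annual% changes in total donations of 8.5% in the West, 5.6% in Quebec, 7.8% in Ontario, and 14.0% in the Atlantic Provinces".
- **Columns of Table 3:** Δ is given first as a rate (per million, six months), then as a donor count headed as yearly, then as a yearly percentage relative to 2011. Footnote 3 repeats that all three are changes in slope.

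The time unit of the slope is not written out anywhere.

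**The concern.** A slope has two units: that of the outcome and that of the time axis. Here the outcome is a half-year rate and the axis runs in half-years, so Δ is a change in the half-year rate per half-year. Expressing it as a yearly change in a yearly count takes two factors of 2: one because a year's count covers two half-years, and one because a year contains two steps of the slope. Table 3 applies only the first.

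The sentence with the four percentages is the plan's plain-language statement of what the primary analysis can detect. If it is out by a factor of two, the study looks twice as sensitive to yearly change as it is. A null result could then be taken to rule out effects that the study had little power to see.

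**Working it through.** **Inputs.** Δ, counts and percentages are from Table 3. Regional populations and 2011 donor totals are not printed and are back-calculated. The Background section gives 2011 DCD rates and shares for Ontario and Quebec, which serve as an outside check. Regional mean square errors are not given.

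**Step 1: reproduce Table 3.** Assume count = 2 × Δ × population, so population (millions) = count / (2Δ). The 2011 total is count / percentage.

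| Region | Population, r = 0.4 | Population, r = 0.8 | 2011 total, r = 0.4 |
|---|---|---|---|
| West | 10.0/(2 × 0.47) = 10.64 | 14.9/(2 × 0.70) = 10.64 | 10.0/0.085 ≈ 118 |
| Quebec | 7.7/(2 × 0.48) = 8.02 | 11.7/(2 × 0.73) = 8.01 | 7.7/0.056 ≈ 138 |
| Ontario | 17.1/(2 × 0.64) = 13.36 | 25.4/(2 × 0.95) = 13.37 | 17.1/0.078 ≈ 219 |
| Atlantic | 5.9/(2 × 1.25) = 2.36 | 8.8/(2 × 1.87) = 2.35 | 5.9/0.140 ≈ 42 |

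The two autocorrelation columns agree. The implied 2011 rates are 138/8.02 ≈ 17.1 donors per million per year in Quebec and 219/13.36 ≈ 16.4 in Ontario. The Background figures give 1.6/0.095 = 16.8 and 3.1/0.20 = 15.5. Had the factor been 4, the populations would halve and these rates would be about 34 and 33. So the factor used was 2, and the table reproduces.

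**Step 2: annualise a slope on six-month steps.** Yearly change in the yearly count = Δ × 2 (half-years per yearly count) × 2 (steps per year) × population, which is twice the printed count.

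| Region | Printed, r = 0.4 | Per year, r = 0.4 | Printed, r = 0.8 | Per year, r = 0.8 |
|---|---|---|---|---|
| West | 10.0 (8.5%) | 20.0 (17.0%) | 14.9 (12.6%) | 29.8 (25.2%) |
| Quebec | 7.7 (5.6%) | 15.4 (11.2%) | 11.7 (8.5%) | 23.4 (17.0%) |
| Ontario | 17.1 (7.8%) | 34.2 (15.6%) | 25.4 (11.5%) | 50.8 (23.0%) |
| Atlantic | 5.9 (14.0%) | 11.8 (28.0%) | 8.8 (21.0%) | 17.6 (42.0%) |

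**Step 3: is Δ per half-year or per year?** Generalised least squares with 24 + 6 points, AR(1) errors at r = 0.4, post-intervention time coded 1 to 6 and a 2-df test (non-centrality 9.63 for 80% power) gives the residual SD that each printed Δ implies. This is about 1.61 × Δ if Δ is per step, and half that if Δ is per year. The comparator is the Poisson SD of the six-month rate, √(2011 total / 2) / population; for the West, √58.8/10.64 = 0.72.

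| Region | SD if Δ is per step | SD if Δ is per year | Poisson SD |
|---|---|---|---|
| West | 0.76 | 0.38 | 0.72 |
| Quebec | 0.77 | 0.39 | 1.03 |
| Ontario | 1.03 | 0.51 | 0.78 |
| Atlantic | 2.01 | 1.00 | 1.95 |

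Per step, the implied noise is near or above Poisson in three regions and about 75% of it in Quebec. Per year, it would be roughly 40 to 65% of Poisson in all four regions at once, which is hard to credit for donor counts.

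**The case against.** **No cell of Table 3 is miscalculated.** This stands. Each count is 2 × Δ × population and each percentage is that count over the 2011 total. If the yearly columns were meant as the yearly-equivalent count for one slope step, they are right and only poorly labelled. The sentence calling them annual changes would still be wrong by a factor of two.

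**The unit of Δ is inferred.** This also stands. If time was coded in years, or the outcome was annualised before modelling, the single factor of 2 is correct and the printed percentages hold. The Outcome measures and Analysis plan sections read against both, and both would need the implausibly small noise of Step 3. That check supports the per-step reading but does not prove it: the mean square errors are not published, the definition of MSE and the coding of post-intervention time are not stated, and Quebec fits only moderately well.

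**A reader might infer that the power result itself is wrong, or that the design must change.** The documents do not support this. The rate column, which carries the simulation result, is untouched, and the outcome, model and test are unaffected. The Analysis plan also commits to confidence intervals for the difference from the counterfactual, so a null result would not be judged from this sentence alone.

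**A reader might also turn six steps of Δ into a percentage above the secular trend.** The projected trend is not given, so that cannot be computed. What follows from Table 3 at r = 0.4 is an excess of 51/34/47/84% of the 2011 count at 6Δ, or about 42/28/39/70% at 5Δ if the first post-intervention point is coded 0. Nor do the UK DCD rates in the Background settle anything, since the primary outcome counts all deceased donors.

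**Conclusion.** The power statement is wrong as written on the most natural reading of the plan. With a half-year outcome on half-year steps, 8.5/5.6/7.8/14.0% at r = 0.4 and 12.6/8.5/11.5/21.0% at r = 0.8 are changes in the annualised count per six-month step. The corresponding year-on-year changes are 17.0/11.2/15.6/28.0% and about 25/17/23/42% of the 2011 count.

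That size depends on one assumption, that time was coded in six-month steps and the outcome was not annualised, which the stated outcome and interval imply. What holds without it is that Table 3 and the sentence after it leave the time unit of the slope unstated. The error lies in annualising and describing the result, not in the calculation of Δ.

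**What to change.** State the time unit of Δ in Table 3. If it is six months, do one of the following:

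1. Relabel the two yearly columns as annualised count, and percentage of the 2011 count, per six-month step, and drop the word annual from the power sentence; or
2. Double the count and percentage columns and the four percentages in the text.

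If a cumulative effect is added, give it as 6Δ (or 5Δ if the first post-intervention point is coded 0) relative to the 2011 count, say which coding applies, and leave out any comparison with UK DCD rates.

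The cost is one table and one sentence. No analysis changes, though under option 2 the stated sensitivity becomes less favourable.

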### Timeline

Objective one (identification and description of: healthcare professional beliefs and attitudes to DCD, specific behaviours and groups requiring changing to increase DCD, and barriers and enablers to DCD) will be completed in year one of the study. Objective two (intervention design) and the intervention implementation will occur in year two of the study. Intervention effectiveness will be assessed in years three through five.

### Ethics

Ethics approval for this study was obtained from the Ottawa Hospital Research Ethics Board (Protocol # 20130635-01H).

## Discussion

The use of DCD in Canada is widely variable and less than that observed in other jurisdictions for reasons that remain unclear. This paper describes a study where we will assess the reasons for these discrepancies nationally to design, implement, and evaluate a theory-based knowledge translation intervention that will aim to increase the number of DCD donors in Canada. This study comprises a detailed and theory-based Canada-wide assessment of stakeholder (clinicians and donor coordinators) beliefs and attitudes to DCD, followed by intervention mapping to design the intervention, and an interrupted times series assessment over three years to evaluate the effectiveness of the developed intervention. This study holds the potential of sharply increasing the number of DCD donors and even perhaps NDD donors available in Canada, which will vastly impact patient health at the population (national) level.

This is the first study to use a behavioural theory approach to define and test novel, theory-based, and ethically-acceptable knowledge translation strategies to increase the numbers of available organ donors. Adopting a behavioural approach will lead to a better understanding of the rationale for specific behaviours related to DCD, resulting in a comprehensive framework on which to develop interventions that may be more successful in increasing the DCD organ donor pool. This study corresponds to Phases zero through three of the UK’s Medical Research Council framework for developing complex interventions [15,16]. The framework developers assert that a successful intervention is more likely when these phases are conducted as part of a larger iterative study (as proposed in this protocol), rather than as sequential studies [16]. They also argue that insights gained during this process can make valuable contributions not only to effecting change in the target population but also to the science of knowledge translation [16]. As far as we know, this will be the first Canadian assessment of the barriers and enablers to DCD. We will also have designed, rolled out across a country and robustly evaluated the effectiveness of a theory-based knowledge translation intervention that addresses these barriers/enablers to improve the number of DCD donors. The results of this study will inform future policy and practice regarding DCD in Canada.

## Abbreviations

CNTRP: Canadian National Transplant Research Program; DCD: Donation after cardiocirculatory death; ITS: Interrupted time series; NDD: Neurological determination of death; PMP: Per million population; TDF: Theoretical domains framework.
